# Vientiane Multigenerational Birth Cohort Project in Lao People’s Democratic Republic: Protocol for Establishing a Longitudinal Multigenerational Birth Cohort to Promote Population Health

**DOI:** 10.2196/59545

**Published:** 2024-11-27

**Keywords:** Lao PDR, birth cohort, growth and development, mental health, dementia, exercise, behavior, aging, intergenerational, noncommunicable disease, hypertension, longitudinal cohort, low- and middle-income countries, maternal health, pregnancy, antenatal care, peripartum, postpartum, child health, infant health

## Abstract

**Background:**

Rapid global population growth and urbanization have led to an increase in urban populations in low- and middle-income countries. Although these urban areas have generally better health outcomes than lower-income rural areas, many environmental, social, and health challenges remain. Vientiane, the capital of Lao People’s Democratic Republic (Lao PDR), has approximately 1.5 of the 7.5 million Laotian population (2022) and provides a unique opportunity to examine health outcomes among socioeconomically diverse populations in the rapidly urbanizing context of the country.

**Objective:**

The aim of the Vientiane multigenerational birth cohort (VITERBI) project is to (1) establish a multigenerational birth cohort in Vientiane capital, Lao PDR, which is representative of the local population, (2) serve as the basis for additional observational (ie, cross-sectional) and intervention studies that promote population health in Vientiane province, and (3) investigate the social, epidemiological, and medical problems of public health importance to Lao PDR.

**Methods:**

VITERBI is a prospective multigenerational birth cohort. The study population is structured around children born between July 1, 2022, and June 30, 2023, who reside in Chanthabuly, Sikhottabong, Sangthong, or Mayparkngum districts of Vientiane. Whenever possible, children and their mothers are enrolled during pregnancy; nonreported pregnancies are enrolled after birth. The cohort plans to enroll 3000 pregnant women and their children and the infants’ fathers, grandparents, and great-grandparents for a total study population of approximately 13,000 individuals. Participants will be followed throughout the life course with a range of data collected, including demographics, behavior, diet, physical activity, physiology, neurodevelopment, health history, quality of life, environmental exposures, depression, anxiety, stress, resilience, household characteristics, obstetric history, birth outcomes, and various living and dementia scales for older adults. Biomarkers collected include height, weight, blood pressure, and hemoglobin levels. Currently, no statistical analyses are planned.

**Results:**

As of April 2024, this study has enrolled 3500 pregnant women and 4579 family members. Study participation is ongoing until May 2025 at minimum, with the goal to extend follow-up until 2050.

**Conclusions:**

The study cohort will be used as a basis for further observational (cross-sectional, longitudinal) and intervention studies. It also serves as a tool to investigate social, epidemiological, and medical problems of public health importance to Lao PDR, which will contribute to broader understanding of regional and international contexts.

**International Registered Report Identifier (IRRID):**

DERR1-10.2196/59545

## Introduction

The Lao People’s Democratic Republic (Lao PDR) is a socialist republic in southeast Asia, bordered by China, Vietnam, Cambodia, Thailand, and Myanmar. In 2018, Lao PDR was home to approximately 7 million people and at least 47 distinct ethnic groups [1]. Roughly half (52.5%) of the population identify as ethnic Lao [1], and one-third (35.6%) live in an urban area [2]. The majority of the urban population reside in the capital city of Vientiane [3]. Historically, Lao PDR’s economy has relied heavily on agriculture; more recently, tourism, foreign investments, and foreign aid have supported Lao PDR’s major economic growth—with an estimated 7% growth rate in gross domestic product between 2011 and 2017 [4]. In 2011, the World Bank changed Lao PDR’s economic status from a low income to lower middle-income economy [5].

Despite the rapid recent economic growth in Lao PDR, many environmental, social, and economic factors contribute to the high rates of mortality and morbidity [2]. Lao PDR reports a high incidence of infectious diseases, including malaria [6,7], dengue [8], Japanese encephalitis [9], typhoid [10], and tuberculosis [7,11]. Parasitic diseases endemic to Lao PDR, including schistosomiasis, soil-transmitted and food-borne helminthiases, and taeniasis, are classified by the World Health Organization (WHO) as neglected tropical diseases, and these disproportionately impact impoverished communities and women and children, engendering broader social and economic consequences [12]. Only 55% of the Laotian population has access to safe drinking water, which increases the frequency of preventable water-related diseases [13,14]. In recent decades of economic development, noncommunicable diseases have increased significantly, among which diabetes mellitus, cardiovascular disease, and various cancers are of particular concern in Lao PDR.

Maternal and child health is a strong predictor for population health and the development and sustainability of economies [15]. Lao PDR has the highest maternal mortality rate in Southeast Asia—estimated between 400 and 600 deaths for every 100,000 births from 2000 to 2008 [16]. Approximately 2 in 5 children younger than 5 years have moderate or severe stunting [17]. On average, a child of poor health will have a lower education attainment and earn a lower income, usually following a similar social and health trajectory as the mother [18]. Although the determinants of maternal and child health are vast and multifaceted, epidemiologic research utilizes several indicators to measure the maternal and child health status of a country, such as low birth weight, maternal morbidity, and antenatal or postpartum care attendance [19].

Maternal and child health indicators are useful tools for guiding public health strategies to improve population health; however, collecting data on maternal and child health alone is not sufficient to understand the health needs of populations. Intergenerational health and wealth beyond the mother also directly influence the life course trajectory of children [20-22]. Mental health problems in childhood are directly related to both the parents’ and grandparents’ mental health history and current mental health status [23]. Children born into socioeconomically disadvantaged families are more likely to have problems with language and reasoning, and similar challenges are found among family members within 2 generations of the family lineage [24]. Epigenetic modifications for various diseases, including gestational diabetes, are impacted by both family genetic backgrounds and environmental factors [25], highlighting the importance of combining intergenerational and individual maternal and child health data.

To date, only a few cohorts exist in Lao PDR or Vientiane. A prospective, community-based cohort study in Vientiane (N=4885 participants, 995 households, 25 villages) was conducted from 2015 to 2016 to monitor influenza-like illnesses and its causative pathogens [26]. Another prospective cohort study in Vientiane (n=1000 pregnant women) was conducted from 2013 to 2015 to investigate the association between maternal morbidity, small for gestational age, and fever [27]. To the best of our knowledge, there are currently no active cohort studies covering all age ranges in this setting.

Our Vientiane multigenerational birth cohort (VITERBI) is the first multigenerational birth cohort created in the urban and semiurban districts of Vientiane capital, Lao PDR, focused on intergenerational health and life course trajectories of children, their parents, grandparents, and great-grandparents. Cohort data will be analyzed to quantify key health challenges and gaps across population groups, ultimately to develop interventions and social impact programs for the improvement of population health.

VITERBI has 3 main aims:

Establish a multigenerational birth cohort in Vientiane capital, Lao PDR, which is representative of the local population.Serve as the basis for additional observational (ie, cross-sectional) and intervention studies that promote population health in Vientiane province.Investigate the social, epidemiological, and medical problems of public health importance to Lao PDR, including intergenerational prevalence of overnutrition and undernutrition, access to antenatal care, adult access to health care, prevalence and predictors of communicable and noncommunicable diseases within families, the current status of geriatric care, and its socioeconomic determinants.

## Methods

### Study Design

The VITERBI cohort will be established in the Vientiane capital of Lao PDR and is a prospective longitudinal birth cohort study enrolling children (during pregnancy), their parents, and relatives up to 3 generations (maternal and paternal grandparents and great-grandparents). Four districts of Vientiane capital were purposely selected based on overall socioeconomic status: Chanthabuly and Sikhottabong are 2 districts located in urban areas of high socioeconomic status, while Sangthong and Mayparkngum are 2 districts located in the semiurban, less developed areas of low socioeconomic status.

### Participants

The target sample size for the VITERBI cohort is 3000 children and their relatives (~13,000) across 4 selected districts. Index women (ie, pregnant women and the first participant enrolled within a family) are eligible for recruitment if they live in Vientiane capital in 1 of the 4 study districts; had an expected due date or gave birth between July 1, 2022, and June 30, 2023; do not plan to permanently move outside the study area; do not have a medical, intellectual, or psychological disability; and agree to participate with a signed informed consent. If the participant is younger than 18 years, a legal representative will additionally need to sign the informed consent. Whenever possible, women will be enrolled during pregnancy; however, women who were not enrolled during pregnancy will be enrolled shortly after birth by using a modified late enrollment questionnaire.

Index women are tracked with a unique VITERBI ID number within the project database. All subsequent family ID numbers retain the number associated with the index woman in addition to their specific unique ID (Figure 1). Thus, all unique personal ID numbers assigned to family members of the child will be associated with the original ID number of the index woman. The ID numbers also indicate the district of residence of the index woman.

Enrollment data from each family member will be used to construct a family tree based around the index woman and child (Figure 2). All enrolled members will be followed up for a minimum of 1 year, with the ambition to extend the follow-up period until 2050. Members of the established cohort will also be recruited and enrolled into additional studies, as they arise.

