Women who were not enrolled during pregnancy are enrolled postpartum to increase enrollment coverage. Birth records are obtained from central hospitals and local health centers to identify recent births that occurred within the cohort window. Staff attempt to contact these women who were neither enrolled nor declined a previous recruitment attempt during pregnancy. Study staff also obtain vaccination records from central health entities to cross-check infant enrollment with both on-time and postpartum recruitment and attempts to recruit women who do not appear in either channel (Figure 3). Access to these records is facilitated by the Lao Tropical and Public Health Institute through the Ministry of Health. Formal birth records obtained from hospitals and vaccination records from the National Immunization Program are used to evaluate recruitment rates. Increasing the overall enrollment coverage of eligible women (prepartum and postpartum) assures that the cohort represents the target population.

Index woman enrollment is the cornerstone for subsequent enrollment of the child’s relatives. In the field, VITERBI staff work closely with the index women to construct family trees detailing relatives of the child who are alive, eligible (living in the 4 study districts), and available to take part in the study. The family tree document guides staff recruitment efforts by providing basic demographic (name, age, and relationship to the child) and contact information of all family members who can be included. As we recruit additional family members, we anticipate their input will continue to guide recruitment and interview of subsequent members by reviewing the family tree document.

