### Data Collection Instruments

The VITERBI study has a total of 6 questionnaires: (1) child enrolled during pregnancy (ie, index women), (2) child enrolled after birth (late enrollment), (3) postpartum form to collect birth outcomes, (4) adult questionnaire for the child’s father, grandparents, and great-grandparents, (5) a short questionnaire for family members who are incapacitated or have a cognitive impairment, and (6) household characteristics. Table 1 shows extensive information about the data collection instruments. All surveys are administered in-person via tablets by trained staff in the field and uploaded remotely to a web-based server at the end of the workday. Each questionnaire is briefly described below but can be accessed by reasonable request.

**Table 1 table1:** Data collection for each participant in the Vientiane multigenerational birth cohort (VITERBI).

Question type			Participants										
			Index mother		Late enrollment		Index mother postpartum		Adult^a^ (<60 years)		Adult^a^ (≥60 years) with no cognition problem		Adult^a^ (≥60 years) with cognition problem
Demographics			✓		✓				✓		✓		✓
Employment			✓		✓				✓		✓		
Obstetric history			✓		✓				✓^b^		✓^b^		
Antenatal care			✓		✓								
Prenatal supplementation			✓		✓								
Tobacco use			✓						✓		✓		
Alcohol consumption			✓						✓		✓		
General diet			✓						✓		✓		
Dietary salt			✓						✓		✓		
Handwashing practices			✓						✓		✓		
Raw food consumption			✓						✓		✓		
Physical activity			✓						✓		✓		
Transportation			✓						✓		✓		
Sedentary behavior			✓						✓		✓		
Pattern recognition and digit span			✓						✓		✓		
Disability			✓						✓		✓		
History of raised blood pressure			✓						✓		✓		
History of diabetes			✓						✓		✓		
History of raised cholesterol			✓						✓		✓		
History of cardiovascular disease			✓						✓		✓		
Experience of pain and arthritis			✓						✓		✓		
Chest pain			✓						✓		✓		
Cervical cancer screening			✓						✓^b^		✓^b^		
Health history			✓						✓		✓		
Environmental exposure			✓						✓		✓		
Family survival history			✓		✓				✓		✓		
Quality of life			✓						✓		✓		
Depression, anxiety, stress			✓						✓		✓		
Resilience			✓						✓		✓		
Recent birth outcomes					✓		✓						
Breastfeeding initiation, exclusivity, duration					✓		✓						
Postpartum depression					✓		✓						
Postpartum medical visit					✓		✓						
Instrumental Activities of Daily Living Scale											✓		✓
Activities of Daily Living													✓
Revised Hasegawa Dementia Scale											✓		✓

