### Statistical Analyses

The main goal of our study is to provide descriptive epidemiologic information on the current health status of a representative, purposive sample of children and their families in Vientiane province, Lao PDR. This includes incidence and prevalence estimates, geospatial maps displaying disease distributions, and factors of health and health behaviors (ie, accessing health care). Currently, no statistical analyses are planned. However, any additional research study will submit a separate institutional review board application.

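### Index women with a disability are excluded without a stated threshold, so maternal disability prevalence is truncated and the cohort cannot be called representative without qualification

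*Protocol article*

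**What the plan says.** Under Methods, Participants, an index woman is eligible only if, among other conditions, she is among those who "do not have a medical, intellectual, or psychological disability". The section gives no definition, severity threshold or assessor. Signed consent is listed as a criterion of its own.

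Three places claim representativeness:
- The first aim in the Introduction: "Establish a multigenerational birth cohort in Vientiane capital, Lao PDR, which is representative of the local population".
- Recruitment, where raising coverage of eligible women is said to be what "assures that the cohort represents the target population".
- Statistical Analyses: "The main goal of our study is to provide descriptive epidemiologic information on the current health status of a representative, purposive sample". That section adds: "This includes incidence and prevalence estimates".

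The third aim in the Introduction includes "prevalence and predictors of communicable and noncommunicable diseases within families". Table 1 (Data Collection Instruments) ticks a row for disability, the row "Depression, anxiety, stress", and rows for history of raised blood pressure, diabetes, cholesterol and cardiovascular disease for index mothers enrolled in pregnancy.

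On how families enter, Recruitment says: "Index woman enrollment is the cornerstone for subsequent enrollment". Relatives must be alive, live in the study districts and be available. No disability exclusion is stated for them, and a short form exists for relatives who are incapacitated or cognitively impaired.

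**The concern.** Eligibility is conditioned on something the study then measures. This is plainest for the disability row of Table 1: women who have the characteristic are, as written, not to be enrolled, so its prevalence among those enrolled cannot describe mothers in the four districts.

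Full coverage of eligible women does not help, because the missing women are outside the definition of eligible. The Recruitment argument that coverage secures representation therefore fails for this group.

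The restriction also falls on one generation only. Mothers are screened on disability while fathers, grandparents and great-grandparents are not, so comparisons across generations rest on different selection rules. Excluding the mother also removes the child and the relatives who would have entered through her. The article neither justifies the criterion nor lists it as a limitation, and it does not say that excluded women will be counted. The cohort is meant to run to 2050 and already feeds other studies, so an unstated restriction would carry into them.

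**Working it through.** **Figures in the document.** There is no stated prevalence, exclusion share or precision target to reproduce. The usable inputs are the targets of 3000 children and about 13,000 people (Abstract; Participants). The true prevalence p and the share s of affected women who are excluded are assumptions.

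**Step 1: prevalence seen among enrolled women.** Excluding a share s of affected women leaves p(1 − s) affected out of 1 − ps:

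observed = p(1 − s) / (1 − ps)

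| Assumed p | Assumed s | Calculation | Observed |
|---|---|---|---|
| 10% | 20% | 0.08 / 0.98 | 8.2% |
| 10% | 50% | 0.05 / 0.95 | 5.3% |
| 10% | 80% | 0.02 / 0.92 | 2.2% |
| 5% | 50% | 0.025 / 0.975 | 2.6% |
| 1% | 25% | 0.0075 / 0.9975 | 0.75% |
| any | 100% | 0 | 0% |

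**Step 2: comparison with sampling error.** The 95% half-width is 1.96 × √(p(1 − p)/3000).
- p = 5%: half-width 0.78 points. With s = 50% the bias is 2.6 − 5.0 = −2.4 points, about three times the half-width.
- p = 1%: half-width 0.36 points. With s = 25% the bias is −0.25 points, inside sampling error.

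So the bias can be dominant or minor, depending on inputs the document does not give. The half-widths use the full 3000. Table 1 does not tick the disability or mental-health rows for late enrolment, so fewer mothers will contribute and the real intervals will be wider.

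**Step 3: families lost.** Women excluded per 3000 enrolled = 3000 × ps / (1 − ps). On the targets there are 13,000 / 3000 = 4.33 people per family.
- p = 10%, s = 50%: 3000 × 0.05 / 0.95 = 158 women, and 158 × 4.33 ≈ 684 people.
- p = 1%, s = 100%: 3000 × 0.01 / 0.99 = 30 women, and about 131 people.

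**Step 4: relatives.** Bias here is indirect, through family clustering. Suppose 5% of families are dropped, prevalence in relatives is 10% in retained families, and it is 1.5 or 3 times that in dropped families. The full-population value is then 0.95 × 10% + 0.05 × 15% = 10.25%, or 0.95 × 10% + 0.05 × 30% = 11.0%. The bias is −0.25 to −1.0 points.

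**Step 5: what a count of exclusions would give.** With p = 10% and s = 50%, 3000 enrolled women include 158 cases and 158 further women were excluded. Adding the excluded women as cases gives (158 + 158) / (3000 + 158) = 10.0%. If the women excluded for that condition are known, the range from 5.3% to 10.0% can be reported instead of 5.3% alone.

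**The case against.** The strongest reply is that the criterion was probably meant narrowly, as an impairment that prevents participation. It stands next to the consent requirement, and Table 1 ticks a disability row and chronic-disease rows for index mothers, so some such women were evidently expected. An article condenses a fuller protocol, and an operational definition may sit there. The Statistical Analyses section also says that no statistical analyses are currently planned.

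Part of this stands. A reader might infer several stronger points that the document does not support:
- **That the aims name disability and mental ill-health.** They do not. Both are measured in Table 1 and fall under the general goal of describing health status; only communicable and noncommunicable disease prevalence is a named aim.
- **That chronic-disease prevalence in mothers is shown to be biased.** The criterion speaks of disability, not disease. Truncation follows only where a disease was treated as a medical disability.
- **That all maternal depression is screened out.** Postpartum depression is assessed after birth, so new cases in women enrolled during pregnancy are kept.
- **That the existing short form could repair the maternal estimates.** In Table 1 it is shown only for adults aged 60 or older with a cognition problem. It covers demographics, daily-living scales and the dementia scale, with no disability, mental-health or chronic-disease module. Consent through a representative is described only for minors.
- **That reopening eligibility would recover the missing families.** The birth window closed on June 30, 2023, and 3500 women were enrolled by April 2024.

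What does not stand is that the narrow reading removes the conflict. Consent is already a separate criterion, the wording carries no link to capacity, and staff teams assigned to separate districts had to apply it. Nor does the absence of planned analyses help: the same section makes prevalence of health status the main goal.

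**Conclusion.** The point holds in limited form. As written, the plan truncates maternal disability prevalence directly, truncates mental-health and chronic-disease prevalence as far as those conditions were treated as a disability, and removes the child and relatives linked to each excluded woman. The unqualified representativeness claims in the Introduction, Recruitment and Statistical Analyses are not supported by the design.

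The direction of the maternal bias is downward. Its size is unknown: the span from 8.2% to 2.2% for a true 10% rests wholly on assumed exclusion shares of 20% to 80%, and at a true 1% with few exclusions the bias would be within sampling error. Effects on relatives are indirect and smaller in the illustrations. This is a matter to correct in the stated target population and in reporting; it does not invalidate the cohort.

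**What to change.** 1. In the Introduction aims, Recruitment and Statistical Analyses, limit the representativeness claim and the maternal prevalence claims to families of women who passed this criterion.
2. In Recruitment, drop the statement that coverage of eligible women secures representation of the target population.
3. State how the criterion was applied: what counted as a disability, who judged it, and whether practice differed between districts.
4. Tabulate the women excluded under it, with the reason, where recruitment records allow. The article does not say that reasons were recorded; if they were not, say so.
5. Report maternal disability and mental-health prevalence with a sensitivity range. Its extreme upper bound counts each excluded woman as a case only of the condition for which she was excluded, not of every condition.
6. For any further enrolment or a successor cohort, limit the exclusion to inability to consent or to complete the interview.

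The cost is a narrower stated target population and some work on the records. Items 1 to 5 need no new data collection from participants.
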